## Abstract

**Background:**

Evidence-based patient information (EBPI) has been recognised as important tool for informed choice in particular in the matter of preventive options. An objective, on the best scientific evidence-based consumer information about subthreshold elevated blood glucose levels (impaired fasting glucose and impaired glucose tolerance) and primary prevention of diabetes, is not available yet. Thus we developed a web-based EBPI and aim to evaluate its effects on informed decision making in people 50 years or older.

**Methods/Design:**

We conduct a web-based randomised-controlled trial to evaluate the effect of information about elevated blood glucose levels and diabetes primary prevention on five specific outcomes: (i) knowledge of elevated blood glucose level-related issues (primary outcome); (ii) attitudes to a metabolic testing; (iii) intention to undergo a metabolic testing; (iv) decision conflict; (v) satisfaction with the information. The intervention group receives a specially developed EBPI about subthreshold elevated blood glucose levels and diabetes primary prevention, the control group information about this topic, available in the internet.

The study population consists of people between 50 and 69 years of age without known diabetes. Participants will be recruited via the internet page of the cooperating health insurance company, Techniker Krankenkasse (TK), and the internet page of the German Diabetes Centre. Outcomes will be measured through online questionnaires. We expect better informed participants in the intervention group.

**Discussion:**

The design of this study may be a prototype for other web-based prevention information and their evaluation.

**Trial registration:**

Current Controlled Trial: ISRCTN22060616.

## Background

Options for primary prevention require very careful consideration and value-neutral information, because a previously healthy population is defined as needing treatment and considered over a long period of preventive measures. Primary prevention of diabetes is much debated. Evidence-based patient information (EBPI) tailored to their needs, should be available for all consumers, because it is essential for informed choice and shared decision-making in the matter of screening procedures and preventive or treatment options [1-3]. Relating to early diagnosis, evidence-based patient information should enable the estimation of the personal risk and therefore giving a basis to the patient to estimate potential and consequences. EBPI on subthreshold elevated blood glucose levels (impaired fasting glucose, IFG, and impaired glucose tolerance, IGT) is not available yet. Since the concept of prediabetes is discussed intensively and identified of high relevance to public health we developed a web-based EBPI [4]. The development of the EBPI followed the accepted steps of EBPI development [3]: 1) systematic literature search performed by two researchers ([name]), 2) selection of relevant publications using predefined inclusion and exclusion criteria, 3) critical appraisal of the literature, 4) translation of the main results into information relevant for consumers using risk communication techniques, 5) and careful piloting of the EBPI within focus groups.

Subthreshold elevated blood glucose levels are characterised as impaired glucose tolerance (IGT) or impaired fasting glucose (IFG). These are risk factors for type 2 diabetes mellitus [5]. IFG and/or IGT were found in a frequency up to 25% in the older population in Germany [6]. The standardised (age and sex) incidence rates of Type 2 diabetes in this population (95% CI) per 1,000 person-years were 15.5 (12.6-19.1) in the total cohort, 20.2 (15.6-26.1) in men and 11.3 (7.9-16.1) in women [7]. Hence, a screening for elevated blood glucose levels might allow identifying a target group for primary prevention of diabetes mellitus. Randomised controlled trials in Finland and the USA suggest a reduction of diabetes mellitus diagnoses in people with subthreshold elevated blood glucose levels through lifestyle-interventions [8,9].

In this study, we aim to optimise the information on elevated blood glucose levels and diabetes primary prevention provided for people 50 years or older by a carefully developed and piloted EBPI. We aim to investigate if an EBPI could improve the decision making process.

## Methods/Design

### Development of the evidence-based patient information

The development of the EBPI followed the accepted steps of EBPI development [3]: 1) systematic literature search performed by two researchers ([name]), 2) selection of relevant publications using predefined inclusion and exclusion criteria, 3) critical appraisal of the literature, 4) translation of the main results into information relevant for consumers using risk communication techniques, 5) careful piloting of the EBPI within 41 participants in several focus groups.

### Study design and setting

Pilot testing covered feasibility and acceptability testing of the instruments and procedures. The testing of the instruments took place via focus groups (15 participants) and via postal evaluation (31 participants). Procedures were tested online in several passes, primarily among employees of the participating project partners. In October 2009, the information has been made available to the study population via web-based assess. We invite visitors of the internet pages of the cooperating health insurance company, Techniker Krankenkasse (TK), and the German Diabetes Centre to take part in the study. Incentives such as books and wellness funds are drawn in order to increase the response rate. Individuals who agree to participate and give their informed consent are randomly assigned to the experimental (evidence-based consumer information) or the control group (standard information). Randomisation is stratified according to sex and age.

#### Intervention

Participants are presented either internet-based EBPI (experimental group) or standard information (control group). A widely used brochure published in the internet and two articles of popular websites are used as standard information on subthreshold elevated blood glucose levels or diabetes [10-12]. The standard information offers information about prevention, early detection, sequelae and treatment of diabetes mellitus. The EBPI summarises the existing knowledge from the scientific literature on the topic.

#### Study population: Inclusion and exclusion criteria

Visitors of the above mentioned two internet pages are invited to participate and to answer online questionnaires when they are aged 50 to 69 years and without known diabetes. Participants who mention to have a diagnosis of type 2-diabetes mellitus are excluded before the statistical evaluation.

#### Study execution

Participants obtain the internet information (EBPI or standard, respectively) on blood glucose disorders, metabolic testing (diabetes-testing) and prevention strategies. The survey is carried out at three points in time (T0/T1, T2), with the first two times during one visit to the website. T0 or T1 is the questioning before or after reading the information, so that the gain of knowledge and a characterisation of later drop-outs is ascertainable. T2 is the online follow-up survey two weeks after the first online session (see Figure 1).

**Figure 1 F1:**
[figure not shown]
**Progress of intervention**.

The variables of the T0-survey and some user behaviour, e.g. point where participants quit the study, will be recorded for later drop-out-analysis.

#### Outcomes

In this study five outcomes will be measured: (i) knowledge of elevated blood glucose level-related issues - the main outcome of the study; (ii) attitudes to a metabolic testing; (iii) intention to undergo a metabolic testing; (iv) decisional conflict; (v) satisfaction with the information. All outcomes will be assessed using self-completed online questionnaires. All translated or newly developed instruments have been carefully piloted based on accepted focus group procedures [13-17].

The main outcome 'knowledge' will be assessed using an eight-item multiple-choice-scale about the benefits and risks of blood glucose screening. Because there is no German version of a validated instrument on this topic available, we developed an own questionnaire based on Anglo-American and German instruments [18-23]. The questionnaire is adapted to the EBPI and displays the knowledge needed to make an informed choice about blood glucose testing.

Attitudes to a metabolic testing (screening test about elevated blood glucose) are determined by a four-item scale [24].

Intention to undergo metabolic testing within the next 12 months: This will be assessed using a single item question (translated into German) with a five point response scale, according to Gattellari et al 2003 [25].

Decisional conflict is measured using the decisional conflict scale (DCS). This is a 16 item scale which elicits uncertainty in choosing among health-related alternatives, contributing factors to uncertainty and the perceived effective decision making. It discriminates between subjects who make and who delay decisions. The five-point Likert scale is anchored by "strongly agree" and "strongly disagree". The DCS has met acceptable standards of reliability and validity [26,27]. A German authorised translation which has been already used in comparable studies, is available [28]. Because the measure is conducted before a decision is made, we set aside the four items which target the situation after the decision. This approach is similar to an earlier evaluation [29].

Satisfaction with the information and the information available is surveyed each with an according question using school grades.

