#### Further variables

Personal data (age, sex, socio-economic variables, life satisfaction) are also assessed. A short instrument has been developed on the basis of recommendations of the German Society of Epidemiology [30]. To assess life satisfaction, a single question from the socio-economic panel is applied [31]. A scale in the form of a 10 rung ladder is used to measure subjective social status [32]. Furthermore, subjects are asked for their medical history, in particular, diabetes mellitus. Participants are also asked if they already passed a blood glucose test.

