#### Statistical analysis

Data of all randomised participants excluding those with self-documented diabetes will be evaluated. The primary analysis will be performed on the study population of T1 compliers with non-missing primary outcome of knowledge. The secondary analysis set will be the subset of compliers of T1 and T2.

The persons who have prematurely terminated the study without completely documented knowledge outcome of T1 will be compared with the study population on the basis of the parameters which are assessed before randomisation (age, sex, education, life satisfaction, and pre-study knowledge about elevated blood glucose), using appropriate statistical tests (chi-square test, Fisher's exact test, t-test or Wilcoxon test). Furthermore, the subgroup of the T1/T2 compliers will be compared with the study population of T1 compliers in a similar manner.

Outcomes will be compared between intervention and control group on an 'intention to treat' basis. For the description of the population in terms of relevant basic parameters - according to distribution - frequency tables, prevalences with 95% confidence intervals or mean values with standard deviations will be calculated. Scores on knowledge and quality of the decision and satisfaction will be evaluated by average scale scores with standard deviations and percentiles. The estimates will be carried out in the intervention and control group respectively in total and stratified for relevant subgroups, e.g. age (40-49 years or older) and sex. To test any effects of the intervention, statistical comparisons will be performed - according to distribution - by chi-square or Fisher's exact test, t-test or Wilcoxon's rank sum test. The tests for each target variable is to be defined before the evaluation.

The primary outcome is an ordinal score with values 0-8. The distributions between intervention and control group will be compared primarily by Wilcoxon's rank sum test. In a secondary analysis the outcome "good knowledge" is defined by dichotomisation of the ordinal knowledge score using a predefined cut point of 5 (≥ 5 versus <5). Intervention and control group will be compared by chi-square test.

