The association between this primary outcome and predictors is estimated using multiple ordinal logistic regression models. A continuation-ratio logit model will be fitted [33]. To simplify the interpretation of the results the scale of the knowledge score will be reduced to 3 ordered values by the predefined classes 0-2, 3-5 and 6-8. The predictors are first examined by univariate models. Then, multiple models considering age, sex, socio-economic variables and participation in a blood glucose test will be discussed.

Then, multiple models considering age, sex, socio-economic variables, participation in a blood glucose test and pre-study knowledge about elevated blood glucose will be discussed. A final multiple regression model will be fitted.

A secondary analysis will be performed on the subpopulation of participants at T1 and T2 considering the ordinal outcomes "attitude" and "intention to undergo uptake a metabolic testing". These variables will be described non-parametrically and control and intervention group will be compared using Wilcoxon's rank sum test.

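### Testing intention is compared by an unadjusted rank test although prior blood glucose testing is recorded; stratifying intention and decisional conflict by it would be a small, nearly free precision gain

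*Protocol article*

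**What the plan says.** All places are in the protocol article.

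- **Entry and exclusion.** Under Study population, people are "invited to participate and to answer online questionnaires when they are aged 50 to 69 years and without known diabetes". Under Statistical analysis, "Data of all randomised participants excluding those with self-documented diabetes will be evaluated". Neither section has a criterion on earlier glucose testing, so people already tested are randomised and analysed.
- **Prior testing.** Under Further variables: "Participants are also asked if they already passed a blood glucose test". No expected share is given, no recency is mentioned, and the survey in which the question is asked is not named.
- **Use of prior testing.** Statistical analysis names it for knowledge only: "The association between this primary outcome and predictors is estimated using multiple ordinal logistic regression models", and "Then, multiple models considering age, sex, socio-economic variables and participation in a blood glucose test will be discussed". It is not a randomisation stratum; the strata are sex and age.
- **Intention.** A single five-point item about the next 12 months. For attitude and intention, in participants of T1 and T2: "These variables will be described non-parametrically and control and intervention group will be compared using Wilcoxon's rank sum test".
- **Decisional conflict.** Under Outcomes, "This is a 16 item scale which elicits uncertainty in choosing among health-related alternatives", shortened for this trial: "Because the measure is conducted before a decision is made, we set aside the four items which target the situation after the decision". The only tests named for it are the general ones, to be chosen by distribution and defined before the evaluation.

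**The concern.** Whether someone has already had a glucose test is likely to relate to how they answer about being tested in the next year and how conflicted they feel about it. The plan accepts prior testing as a predictor of knowledge, but does not name it for the two outcomes that concern the testing decision itself.

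Two things follow. First, if scores differ by prior testing, that difference sits in the unadjusted comparison as noise that could be removed. Second, if the information moves people less when they have already been tested, the pooled effect is smaller than the effect in people not yet tested, and a null result on these outcomes is harder to read. The first is a matter of precision and can be remedied. The second is only a possibility, because the article gives neither the share tested nor any sign of a smaller effect in them.

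**Working it through.** **1. The plan's own figure.** Inputs from Sample size and statistical power: 0.20 SD, two-sided 5%, 90% power. Normal approximation: n = 2(1.960 + 1.282)²/0.20² = 525.4, so 526 per group. The t-test calculation gives 526.3, so 527, as stated. Power at 527 is 90%. This figure is for knowledge. The article gives no effect size or sample size for intention or decisional conflict, and intention is analysed in the T1-and-T2 subset, whose size is not given. 527 and 0.20 SD are therefore borrowed below for illustration only.

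**2. Assumptions.** p = share already tested, taken as 10%, 30%, 50%. s = difference in mean score between tested and untested people, in units of the within-group SD, taken as 0.5 or 1.0. None of these comes from the document. Scores are treated as approximately normal, as the article does for its own power calculation.

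**3. Variance removed by stratifying.** The mixture adds p(1-p)s² to a within-group variance of 1, so the share removed is p(1-p)s² / (1 + p(1-p)s²).

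| p | s = 0.5 | s = 1.0 |
|---|---|---|
| 10% | 0.0225/1.0225 = 2.2% | 0.09/1.09 = 8.3% |
| 30% | 0.0525/1.0525 = 5.0% | 0.21/1.21 = 17.4% |
| 50% | 0.0625/1.0625 = 5.9% | 0.25/1.25 = 20.0% |

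**4. Power if the effect is 0.20 SD in everyone.** Unstratified power is Φ(0.20/√(1 + p(1-p)s²) × √(527/2) − 1.96), with √(527/2) = 16.23. For p = 10%, 30%, 50% this gives 89%, 89%, 88% at s = 0.5 and 87%, 84%, 83% at s = 1.0. Stratified power is Φ(0.20 × 16.23 − 1.96) = 90% throughout.

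**5. Power if the effect is 0.20 SD in untested people and zero in tested people (s = 0.5).** The pooled effect is 0.20(1-p)/√(1 + p(1-p)s²). Stratified power is approximately Φ(0.20(1-p) × 16.23 − 1.96). Untested-only power is Φ(0.20 × √(527(1-p)/2) − 1.96).

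| p | pooled effect | pooled power | stratified, all kept | untested only |
|---|---|---|---|---|
| 10% | 0.18 SD | 82% | 83% | 87% |
| 30% | 0.14 SD | 60% | 62% | 78% |
| 50% | 0.10 SD | 35% | 37% | 63% |

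Stratification still averages over tested and untested people, so it recovers almost none of the power lost to dilution. The larger figures in the last column belong to a different analysis, one that discards tested participants. If tested people share the full effect, that analysis loses power instead: 87%, 78%, 63% against 90%.

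**The case against.** A reader might infer that enrolling people already tested contradicts the reason for dropping the four items, and hence that both outcomes are diluted. The document does not support this. The stated reason concerns timing relative to the decision under study. The intention item looks 12 months ahead and a glucose test can be repeated. The article nowhere says that an earlier test settles the matter, and it gives no share or recency of testing. Nor does the shortening cause any dilution: with all 16 items kept, the mix of tested and untested people would be the same. The intention item does not rest on that reason at all. This objection stands in full.

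It is also tempting to rest the claim for these outcomes on never-tested participants. As described, the question does not separate a recent test from one years ago, so this would drop people whose decision is still open, and the power advantage depends on an assumed zero effect in everyone else. That objection stands too.

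Three further points are fair:

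- The unadjusted Wilcoxon test is valid, and randomisation balances prior testing in expectation.
- A condensed article may leave the decisional conflict test and the subgroup list to a plan not shown. For decisional conflict the point is therefore a recommendation only. For intention, the article does fix the unadjusted test.
- The prior-test question is not in the article's list of parameters assessed before randomisation, so its timing has to be confirmed.

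**Conclusion.** What holds is narrow: a recorded variable, already treated as a predictor of knowledge, is left out of the stated comparison of intention and is not named for decisional conflict. Using it would remove about 2-6% of the variance if tested and untested people differ by 0.5 SD, and 8-20% at 1 SD, for tested shares of 10-50%. In the cases computed, that is worth between under one and about seven percentage points of power, and stratifying was never worse. The shares, the score difference and the effect size are all assumptions.

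Dilution is possible but not shown, and stratifying would not cure it. There is no bias between arms, and the primary outcome and the 527 per group are unaffected. This is a minor improvement for two secondary outcomes.

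**What to change.** Before the evaluation, specify that intention and decisional conflict are each compared between arms by a van Elteren test (a Wilcoxon rank sum test stratified by prior blood glucose test, yes or no), keeping all participants in the analysis set. State how unanswered prior-test questions are handled, for example as a separate stratum, so that nobody is lost. Describe results by prior-test status as supportive only.

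One condition: the answer must come from T0, before the information is read. If the question is asked only afterwards, reading the information could influence the answer, and the unadjusted test should stay.

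Do not restrict the claim to never-tested participants, and leave the item selection of the decisional conflict scale as it is. The cost is a sentence or two in the analysis plan and a check of the T0 questionnaire. No new data or participants are needed.

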#### Further variables

Personal data (age, sex, socio-economic variables, life satisfaction) are also assessed. A short instrument has been developed on the basis of recommendations of the German Society of Epidemiology [30]. To assess life satisfaction, a single question from the socio-economic panel is applied [31]. A scale in the form of a 10 rung ladder is used to measure subjective social status [32]. Furthermore, subjects are asked for their medical history, in particular, diabetes mellitus. Participants are also asked if they already passed a blood glucose test.

#### Randomisation

Randomisation takes place immediately before presentation of the information, deposited on a random number generator. To gain a balanced distribution of the study population characteristics, a stratified block randomisation is conducted (4 strata defined by women/men and 40-49 years/50 years and older, 1:1 randomisation between intervention and controls within each stratum using blocks of size 10).

Crossover between the study groups is not possible, because the IP-addresses of the participants are identified by the system.

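### The stated age range (50-69) contradicts the 40-49 band used for the randomisation strata and the age subgroup; the document does not settle which is right

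*Protocol article*

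**What the plan says.** On who is eligible, the sections agree on a lower limit of 50:

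- The abstract (Methods/Design): "The study population consists of people between 50 and 69 years of age without known diabetes".
- The inclusion criteria invite visitors "when they are aged 50 to 69 years and without known diabetes".
- The aim at the end of the Background concerns information "provided for people 50 years or older by a carefully developed and piloted EBPI".

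On the use of age in allocation and analysis:

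- Study design and setting: "Randomisation is stratified according to sex and age".
- Randomisation: "4 strata defined by women/men and 40-49 years/50 years and older", with "1:1 randomisation between intervention and controls within each stratum using blocks of size 10". The stated purpose is balance of the population's characteristics between the arms.
- Statistical analysis: estimates by arm, in total and "stratified for relevant subgroups, e.g. age (40-49 years or older) and sex".

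The Statistical analysis section names self-documented diabetes as the only eligibility-type exclusion from the data of those randomised. It names none by age. The multiple regression models planned later in that section include age.

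**The concern.** Both age cuts sit at 50, which is the lower limit of eligibility, and both name a band that lies wholly outside the eligible range. The band appears once for allocation and once for analysis, so it does not look like a single typing slip. No sentence makes people aged 40-49 eligible or explains the cut.

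Either way the plan cannot be followed as described. If the age limit holds, the age factor has only one level: the age balance that the design claims is not delivered, and the age subgroup has nobody on one side. If the strata are right, the population named in the abstract and inclusion criteria is not the one randomised, and results presented for people of 50 or older would rest partly on younger people. Recruitment opened in October 2009, so the answer bears on data already being collected.

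**Working it through.** **1. Stated strata.** Inputs from the Randomisation section: 2 sexes and 2 age bands. 2 x 2 = 4, which reproduces the stated number.

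**2. Strata that can fill under the stated eligibility.** Ages 50 to 69 are 20 single years of age. Sorting them into the stated bands gives:

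| Stratum | Eligible years of age in it |
|---|---|
| Women 40-49 | 0 |
| Men 40-49 | 0 |
| Women 50 and older | 20 |
| Men 50 and older | 20 |

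Two of four strata are empty. The two that remain differ only by sex. In the age subgroup, one level has n = 0 and the other is the whole trial.

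**3. Size of the lost age balance, if 50-69 is enforced.** Age within 50-69 is left to chance. Take n = 527 evaluable per arm (Sample size and statistical power). The share p aged 60-69 is not given, so it is an assumption. The 95% range of the difference in that share between arms is

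±1.96 x sqrt(2p(1 - p)/n)

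- p = 0.5: sqrt(2 x 0.25/527) = 0.031; x 1.96 = 0.060, about ±6 percentage points.
- p = 0.2: sqrt(2 x 0.16/527) = 0.025; x 1.96 = 0.048, about ±5 percentage points.

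**4. What that could do to the primary outcome.** Suppose, again as an assumption, that knowledge differs between the two decades of age by 0.3 to 0.5 SD. At the 6-point limit, the shift between arms is 0.06 x 0.3 = 0.018 SD to 0.06 x 0.5 = 0.030 SD. Against the 0.20 SD target difference that is 9% to 15%. It is random in direction, so it is not bias.

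**5. Sample size.** For a difference of 0.20 SD, two-sided 5% and 90% power, the normal approximation gives 526 per group. The t-test gives 526.3, rounded up to 527, as stated. The strata do not enter this calculation, so it is unaffected.

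**6. The other reading.** If people aged 40-49 are admitted, no stratum need be empty. The analysis rule then decides who counts: all randomised participants other than those with self-documented diabetes, and for the primary analysis those with a complete knowledge score at T1. Nothing in that rule removes a person aged 40-49.

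**The case against.** The strongest reply is that little statistical harm follows. With 50-69 enforced, the empty strata are inert: blocked 1:1 allocation within each sex is sound, and the primary test keeps its validity. The chance imbalance in age is small, as shown above. Stratifying at entry would not guarantee balance in the evaluable set anyway, because drop-out occurs after randomisation. Age is already in the planned regression models. The age subgroup is offered only as an example of a split for descriptive estimates; no confirmatory subgroup test or interaction is specified. With more than 1,000 participants, stratifying by age is optional. All of this stands, and it limits the severity.

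It does not remove the contradiction. The primary Wilcoxon test does not use the age term in the models, and none of these replies says who is in the trial.

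A reader might go further and infer that half the strata are in fact empty and that the age stratification does nothing. The document does not support that as a fact. It describes no age check at entry, and two separate sections use the 40-49 band, so the error could lie in the eligibility statement instead. Nor does it support a claim that the primary comparison is compromised under the 50-69 reading.

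**Conclusion.** The contradiction is certain; which side is wrong is not. Two consequences follow, each conditional.

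- **If 50-69 is enforced:** two of four strata and one of two subgroup levels are empty, allocation is stratified by sex alone despite the description in Study design and setting, and age-specific estimates at that cut cannot be produced. The imbalance left to chance is about ±5 to ±6 percentage points under the assumed shares aged 60-69. Type I error and sample size of the primary comparison are unchanged.
- **If people aged 40-49 are randomised:** the stated population is wrong, and those who complete T1 enter the primary analysis. Their number cannot be judged from the document.

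This is an internal inconsistency that should be fixed before evaluation, chiefly because it leaves open to whom the result applies. It is not a threat to the between-arm comparison.

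**What to change.** State one age range and use it in the abstract, Study design and setting, the inclusion criteria, Randomisation and Statistical analysis. If that range is 50-69:

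- Use an age cut inside it for the subgroup, for example 50-59 and 60-69. That particular cut is a suggestion, not taken from the document.
- Use the same cut for the strata if the randomiser can still be changed. If not, leave allocation as it is, describe it as stratified by sex only, and rely on the age term already in the planned regression models.
- State before evaluation how anyone aged 40-49 already randomised is handled, with the primary analysis restricted to the stated population. Age is recorded before randomisation, so this restriction does not disturb the comparison between arms.

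The cost is a protocol clarification, one line in the analysis plan and, at most, one parameter in the web randomiser. The calculated sample size does not change. If people aged 40-49 were counted towards the 527 per group, that count should be redone within the stated population.
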